Symptom-related discomfort will be measured using the Self-Completed HIV Symptom Index [87]. This 20-item instrument determines using a scale of 1 to 4 whether symptoms are present (0 = absence) and the degree of discomfort experienced. The instrument has been validated on 188 PLHIV, and it was found to have acceptable psychometric properties, including good construct validity.

Social support will be evaluated using the Medical Outcome Survey [88,89]. One dimension of social support will be measured by subscale of emotional support, which has eight item, each of which is rated on a five-point Likert scale. The instrument has been found to have good content validity and appreciable internal consistency.

A sociodemographic questionnaire will cover personal characteristics such as sex, age, family situation, level of education, employment situation, number of children, and questions about HIV, the therapeutic regimen, and presence of symptoms.

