### Recruitment and online data collection

The study will be conducted entirely online. The project will be advertised on the websites of resources available to PLHIV, where a hyperlink and a banner will be inserted to redirect parties interested in participating in the online research. The targeted resources include partner clinics, community agencies, and other organizations that deliver teaching, care, treatment, or follow-up to PLHIV. In addition, health professionals and stakeholders will be invited to inform their PLHIV about the study. To promote the project among PLHIV, different communication strategies will be used: 1) traditional methods, such as poster and information brochures; and 2) technological or virtual methods, by advertising the study on websites of organizations (medical clinics, association for PLHIV) that are often visited by PLHIV.

Individuals who will visit the study’s website will view a short video clip of testimonials by a few PLHIV, then they will be given information on the study. After accepting the conditions of the study and consenting to take part in it, they will sign up for the study by providing an email address and a pseudonym. Each participant will be validated through an email address check. Once this step is completed, a hyperlink will be emailed to allow participants to access the first questionnaire online on the website, and only after having completing this questionnaire will they be randomly assigned by the computer system to the experimental group or the control group. Participants in the control group will be invited to consult pre-determined websites that offer information on ART and its associated side-effects. Participants in the experimental group will be offered the virtual intervention through the web application. At 3 and 6 months after the initial measurement, participants will complete the online questionnaires again. A reminder to this effect will be emailed to them in the days prior to the scheduled measurement. Participants will be compensated for their time spent on the study with a gift certificate for each measurement time completed.

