### Type of analysis used

To establish whether the experimental and control groups are equivalent, the means and medians of the continuous variables and the frequency distributions of the discrete variables will be compared using descriptive analyses. The principal analyses will focus on comparing the two groups in terms of treatment adherence (the study’s main outcome, considered as a binary variable with adherent being ≥ 95% and non-adherent > 95%) at the end of follow-up at T6. An intention-to-treat (ITT) analysis will be carried out to evaluate the true value of the intervention in a real context. Consequently, in the following analyses, all participants will be assessed in their respective randomization group as to whether they are following the procedure or have been lost to attrition during follow-up. In accordance with the principles of ITT, participants who drop out and those for whom there is no adherence measure at T6 will be considered as non-adherent.

The primary hypothesis is that the VIH-TAVIE intervention will increase the proportion of treatment-adherent patients at T6. This hypothesis will be tested using a χ^2^ test with 1 degree of freedom. If preliminary analyses show that the two groups differ on certain characteristics, multivariate logistic regression will be used to adjust the intervention’s effect on these characteristics, which will be considered as potential confounding variables. In this case, the two-tailed Wald’s test will be used to test the intervention’s adjusted effect.

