For the secondary analyses, the two groups will be compared on all the repeated measures of adherence (T3 to T6) using a generalized estimating equation (GEE) approach that generalizes the logistic regression for longitudinal data with repeated measures of the binary measure [90]. We will assume that the covariance matrix has an auto-regressive structure of order = 1 to account for inter-correlations between repeated measures (over the course of follow-up) with the same participants. The difference between repeated measures of adherence (T3 and T6) will constitute the binary dependent variable. The binary intervention indicator, the indicator of time since the follow-ups (3 and 6 months) and, if necessary, the confounding variables, will be included as independent variables. Finally, the interaction between the intervention effect and the time effect will be added to the GEE model and will be tested to verify whether the intervention’s effect on adherence varies over time. In the GEE analyses, a conservative approach will be used and, accordingly, all missing data for the dependent variable (adherence) will be replaced with ‘non-adherent’. The same approach will be used to evaluate the effects of the intervention on the repeated measures of the intermediary variables. However, given that these variables will be measured by means of quantitative scales, a linear mixed model for repeated measures of a continuous dependent variable [91] will be used instead of the GEE model.

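### The primary analysis switches from a chi-square to an adjusted Wald test on an undefined look at baseline imbalance, with no covariates named and no rule on which result counts

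*Protocol article*

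**What the plan says.** All of this is in the protocol article, mostly under 'Type of analysis used'.

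- Primary comparison: "The principal analyses will focus on comparing the two groups in terms of treatment adherence", as a binary variable at T6.
- Named test: "This hypothesis will be tested using a χ^2^ test with 1 degree of freedom".
- Switch: "If preliminary analyses show that the two groups differ on certain characteristics, multivariate logistic regression will be used to adjust" the intervention effect for those characteristics, which are then treated as potential confounders. The sentence that follows reads: "In this case, the two-tailed Wald’s test will be used to test the intervention’s adjusted effect".
- How a difference is judged: means and medians of continuous variables and "the frequency distributions of the discrete variables will be compared using descriptive analyses". No test or threshold is given.
- Candidate variables: the 'Measurement' section gives an open list, "A sociodemographic questionnaire will cover personal characteristics such as sex, age, family situation, level of education, employment situation, number of children", followed by questions on HIV, regimen and symptoms. The scales come on top of that.
- Secondary GEE: the intervention and time indicators are included and, "if necessary, the confounding variables, will be included as independent variables". The intermediary variables are to be handled in the same way, with a linear mixed model.
- Timing, from 'Recruitment and online data collection': participants fill in the first questionnaire, and "only after having completing this questionnaire will they be randomly assigned by the computer system" to a group.

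**The concern.** The rule selects covariates by the wrong property. Baseline is complete before allocation, so differences between the groups are chance. A chance difference does not show that the variable predicts adherence at T6. The rule can bring in variables with no prognostic value and leave out T0 adherence, the obvious prognostic candidate, whenever T0 adherence happens to look balanced.

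The rule is also undefined at three points: what counts as a difference, which variables are eligible, and whether the adjusted result takes the place of the chi-square. Two analysts following the text could report different primary results from the same data. The quantity estimated would change too, from a marginal difference in proportions to a conditional odds ratio.

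At stake are a primary result that is not unique, some room for choosing between results, and possibly some lost power.

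**Working it through.** **1. The plan's own figure.** Inputs from 'Sample': 50% vs 70%, two-sided 0.05, 80% power, chi-square, 20% attrition.

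n per group = [1.96·√(2·0.6·0.4) + 0.8416·√(0.5·0.5 + 0.7·0.3)]² / 0.20² = (1.3579 + 0.5708)² / 0.04 = 93.0.

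That is 93 per group, or 186, and 186/0.8 = 232.5 against the stated 232. The figure reproduces, and it rests on the unadjusted chi-square alone.

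**2. How often chance would fire the trigger.** The document states neither the number of characteristics K nor a threshold, so both are assumed here, with independent characteristics. P(at least one difference) = 1 − (1 − α)^K.

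| K | α = 0.05 | α = 0.20 |
|---|---|---|
| 5 | 23% | 67% |
| 10 | 40% | 89% |
| 15 | 54% | 96% |

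For example, 1 − 0.95^10 = 0.40. The comparison in the plan is descriptive, so these values only illustrate how far the answer depends on the missing criterion.

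**3. Type I error, simulated under no effect with 116 per group.** The T0-T6 association is assumed, because the documents give none. At 50% margins a correlation φ corresponds to an odds ratio of ((1 + φ)/(1 − φ))². φ = 0.3 gives (1.3/0.7)² = 3.4, φ = 0.5 gives 9 and φ = 0.6 gives 16.

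- Chi-square alone: about 5-6%. The exact size at a 50% rate is 5.7%, because of discreteness.
- Strict replacement by the Wald test when T0 adherence differs at p < 0.05: 4.0-5.8%. With one or ten candidate covariates and thresholds of 0.05 or 0.20: 3.4-5.1%.
- Either result claimable, but the adjusted one available only once the trigger is met: 5.4-7.3%.
- Either result claimable whenever wished (chi-square or T0-adjusted): about 6.5-9%.
- One fixed analysis adjusted for T0 adherence: 4.8-5.1%.

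**4. Power under the plan's own missing-data rule.** With 20% lost and scored non-adherent, the rates become 0.8 × 50% = 40% and 0.8 × 70% = 56%, with 116 per group. For the chi-square by the normal approximation:

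- critical difference = 1.96·√(2·0.48·0.52/116) = 0.1286
- SE under the alternative = √((0.40·0.60 + 0.56·0.44)/116) = 0.0648
- (0.16 − 0.1286)/0.0648 = 0.485, which gives power of about 69%.

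Simulated power with losses at random and assumed φ from 0.3 to 0.6 is about 70-72% under the triggered rule (T0 adherence, p < 0.05) and about 72-79% when always adjusting for T0 adherence. The gain runs from almost nothing at φ = 0.3 to about 7 points at φ = 0.6.

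**5. Does the fix need more participants?** At 93 completers per group and 50% vs 70%, the chi-square has about 80% power. Fixed adjustment has about 82%, 86% and 92% for assumed T0-T6 odds ratios of 3, 6 and 15. No increase in N is needed.

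**The case against.** The strongest case against is that a primary test is named, the sample size is built on it, and the adjusted model can be read as supportive. Covariate names and imbalance criteria are also commonly left to a statistical analysis plan, which is not shown here. Part of this stands. Missing detail alone would be no finding. But the article does not merely omit detail. It states a rule that makes the analysis depend on observed imbalance, and an analysis plan that followed it would inherit the problem. Nothing in the text labels the adjusted model supportive, and the phrase introducing the Wald test can just as well mean replacement.

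Two stronger readings are tempting, and the documents do not support them.

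- A reader might infer that the trial has lost control of its type I error. The trigger uses baseline data only, not the T6 outcome, and strict application stays at about 5% or below. The higher range needs a free choice between two results. The text permits that by silence but does not plan it. Part of the gap from 5% also belongs to the chi-square itself.
- A reader might compare power with all 116 per group observed and find 89-90% for the triggered rule against 94-97% for fixed adjustment. That sets aside the plan's 20% attrition and its rule that missing adherence counts as non-adherent. It also uses only strong correlations (0.5-0.6).

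It is also fair to say that keeping the chi-square as the single primary analysis would cure the ambiguity. Adjusting for T0 adherence is the preferred repair, not the only valid one.

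**Conclusion.** The point holds as a defect in the stated rule. The switch depends on chance imbalance, judged without a criterion, over an open list of variables, with no precedence between the two results, and the secondary models carry the same trigger. Confidence in this is high because it rests on the text.

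The numerical consequences are modest and rest on assumptions: the T0-T6 association, the number of characteristics, the threshold, and losses at random. Strict use is about nominal. Inflation to roughly 6.5-9% arises only if either result may be claimed. The power forgone against always adjusting for T0 adherence lies between almost none and about 7 points. The change should be made because it costs nothing and leaves one primary result, not because the trial is invalid without it.

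**What to change.** In 'Type of analysis used':

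1. Delete the sentence that makes logistic regression conditional on observed group differences, and take the conditional confounders out of the GEE sentence quoted above. Apply the same to the mixed models for the intermediary variables.
2. Name one primary analysis in advance. The preferred choice is logistic regression of T6 adherence on group, adjusted for T0 adherence and at most a few named prognostic variables, with the unadjusted chi-square as a supporting analysis.
3. State that any adjustment prompted by observed imbalance is a sensitivity analysis and cannot replace the primary result. Baseline tables remain descriptive.

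The cost is analysis wording only. T0 is already a measurement time and no extra participants are needed. Data collection has started, so the change should be dated and fixed before anyone sees outcomes by group.

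### One sentence in the secondary analysis names the T3–T6 difference as the binary GEE outcome, which contradicts the repeated-measures model described around it

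*Protocol article*

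**What the plan says.** All of this stands in one paragraph of the protocol article, under Type of analysis used.

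- Aim and method: "the two groups will be compared on all the repeated measures of adherence (T3 to T6) using a generalized estimating equation (GEE) approach", a method that "generalizes the logistic regression for longitudinal data with repeated measures of the binary measure".
- Correlation: "We will assume that the covariance matrix has an auto-regressive structure of order = 1".
- Outcome: "The difference between repeated measures of adherence (T3 and T6) will constitute the binary dependent variable".
- Covariates: "The binary intervention indicator, the indicator of time since the follow-ups (3 and 6 months") and, where needed, confounders.
- Time-varying effect: "the interaction between the intervention effect and the time effect will be added to the GEE model".
- Missing data: "all missing data for the dependent variable (adherence) will be replaced with ‘non-adherent".

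The preceding paragraph of the same section treats adherence as a binary variable. The Design section gives three measurement times (T0, T3, T6), two of them after baseline.

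**The concern.** The outcome sentence is the only one whose purpose is to define the dependent variable of this model, and it does not fit the model. The secondary analysis is the only planned between-group comparison of adherence that uses T3, and the only one that tests whether the effect varies over time. If the sentence stays, the analyst must either disregard it or disregard most of the paragraph. The two choices answer different questions: how the groups compare over follow-up, or how much adherence moved between month 3 and month 6. That choice should not be left open until the data are in hand.

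**Working it through.** **Figures in the plan.** No figure is stated for the GEE. The Sample section's planning figure for the primary T6 test does reproduce. For 50% versus 70%, two-sided alpha 0.05 and 80% power, with pooled variance under the null:

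n per group = [1.96·√(2·0.6·0.4) + 0.8416·√(0.25 + 0.21)]² / 0.20² = (1.358 + 0.571)² / 0.04 ≈ 93, so 186 in total.

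186/0.8 = 232.5, against 232 in the plan. None of this depends on the GEE sentence.

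**Step 1: values of the stated outcome.** Let Y3 and Y6 be adherence (0/1) at T3 and T6, and D = Y6 − Y3. D can be -1, 0 or +1. With the same adherence rate p at both visits and within-person correlation rho,

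P(D = +1) = P(D = -1) = p(1 − p)(1 − rho).

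The documents give no rho, so 0.3, 0.5 and 0.7 are assumed. The p values are the planning rates, assumed to hold at T3 as well as T6.

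| rho | control, p = 0.5: -1 / 0 / +1 | experimental, p = 0.7: -1 / 0 / +1 |
|---|---|---|
| 0.3 | 0.175 / 0.650 / 0.175 | 0.147 / 0.706 / 0.147 |
| 0.5 | 0.125 / 0.750 / 0.125 | 0.105 / 0.790 / 0.105 |
| 0.7 | 0.075 / 0.850 / 0.075 | 0.063 / 0.874 / 0.063 |

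Three values are possible, so D is not an outcome for a logistic model.

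**Step 2: records per person.** Two follow-up visits give one D per participant. With one record there is no within-person correlation to estimate, no variation in the 3/6-month indicator, and hence no interaction. Nor can D take the value non-adherent, so the missing-data rule cannot be applied to it.

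**Step 3: what D would measure.** The between-arm contrast in mean D is

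(p6E − p3E) − (p6C − p3C) = (p6E − p6C) − (p3E − p3C),

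which is the risk difference at T6 minus the risk difference at T3. This is a time-by-intervention contrast, not the intervention effect.

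- Equal benefit at both visits (70/70 versus 50/50): (0.70 − 0.70) − (0.50 − 0.50) = 0, whatever the amount of individual switching.
- Waning benefit (assumed 70% then 60%, control 50% at both): (0.60 − 0.70) − 0 = -0.10. The contrast points against the intervention although its adherence is higher at both visits.

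**Step 4: simulated size of the gap.** Settings: 93 per arm, no missing data, equal benefit at both visits, 300 runs per setting. The GEE had intervention and time terms; with two visits AR(1) equals exchangeable correlation. The Monte Carlo standard error is about √(0.05·0.95/300) = 1.3 points near 5% and √(0.9·0.1/300) = 1.7 points near 90%.

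| rho | GEE on status at T3 and T6 | t-test on signed D | test on changed/unchanged |
|---|---|---|---|
| 0.3 | 94% | 4% | 14% |
| 0.5 | 90% | 6% | 9% |
| 0.7 | 88% | 4% | 6% |

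The signed difference rejects at about its type I error rate. The changed/unchanged indicator has probability 2p(1 − p)(1 − rho), which at rho = 0.5 is 0.25 in control and 0.21 in the experimental arm. The arms differ only because p(1 − p) is smaller at 70% than at 50%, and the indicator counts losses of adherence together with gains.

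**The case against.** The strongest reply is that the paragraph largely corrects itself. Its missing-data rule names the dependent variable as adherence and gives it the value non-adherent. The opening sentence, the AR(1) structure, the time indicator and the interaction all describe the usual repeated-measures logistic GEE. One sentence stands against the others, and a competent analyst would probably fit the intended model. This stands, and it limits the severity. It does not remove the point, because the sentence that sets the outcome sets it wrongly.

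A second reply is that the word binary may signal a changed/unchanged indicator. That would be a 0/1 variable, but it still gives one record per person and does not distinguish improvement from deterioration, so it does not rescue the sentence.

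Three stronger readings are tempting and are not supported:

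- A reader might infer that the trial would report no effect when the benefit is sustained. That follows only if someone keeps the signed difference, drops the logistic form, the correlation structure, the time term and the interaction, and uses a test that the plan does not name. Taken literally, the stated model does not return a null result; it cannot be fitted.
- A reader might infer that the main result is at risk. The primary hypothesis is tested by a chi-square test at T6, which this sentence does not touch.
- A reader might infer that the error carries over to the intermediary variables, since the plan uses the same approach for them. The text there names the repeated measures themselves as the outcome of a linear mixed model.

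**Conclusion.** The point holds as an internal contradiction: the stated outcome is incompatible with the model in the same paragraph. That D has three possible values and gives one record per person needs no assumption. The zero contrast under equal benefit is exact for any switching rate, but it rests on assumed T3 rates and applies only if the signed difference were actually tested. The simulated rates (88–94% against 4–6%) rest further on assumed correlations of 0.3 to 0.7 and complete data, and they illustrate rather than forecast. Severity is moderate: a secondary analysis is misdescribed, its intent can be recovered from the surrounding text, and the primary test and sample size stand.

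**What to change.** Replace the outcome sentence with: *Adherence status (adherent / non-adherent) at each of T3 and T6 is the binary dependent variable, with two records per participant.* Keep the intervention, time and interaction terms, the AR(1) structure and the missing-data rule as written; all of them then apply. Any interest in whether the effect changes between T3 and T6 is already served by the interaction term. The cost is one sentence, with no change to data collection, sample size or the primary analysis. It should be settled before the outcome data are analysed.

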## Discussion

### Challenges of an online randomized controlled trial

Carrying out this online RCT poses various challenges, particularly in terms of recruitment, ethics, and data collection, including participant follow-up over an extended period [92].

First, to attract and retain the online participation of PLHIV interested in the study, the team sought the help of web design experts. This help led to the development of a brand image (concept of branding) by an artistic director, who created a logo that would carry the image of the study and be easily recognizable by our target group. This branding set the tone (in terms of color and visuals) for our website pages, which were created to be visually attractive to participants. More specifically, upon reaching the first page of the website, participants will listen to testimonials by a few PLHIV about their own experiences with medication intake and with browsing the web in search of health-related information. Aside from being an interesting and dynamic visual tool, testimonials have been used to allow potential participants to identify with the intervention, and to humanize and personify the web-based study. These testimonials also have the potential to strengthen the branding of the intervention. Then, in a short video clip, the research coordinator and a project spokesperson will present information on the study, including its aim and inclusion criteria, and explain what participation entails.

Various communication strategies will be used to promote the study among PLHIV. First, traditional methods of dissemination will be used, such as publishing advertisements or short articles in magazines aimed at PLHIV, and distributing information brochures and posters to the clinics and community organizations targeted. Second, an internet-based approach will also be used, consisting of posting a hyperlink to our study on the websites of organizations (medical clinics, association for PLHIV, community groups) frequently visited by PLHIV. In this regard, Birnbaum [93] suggested that such organizations should run advertisements in their electronic newsletters. A list of targeted internet media will be compiled in collaboration with key informants working with PLHIV in community organizations. There are other methods of online recruitment, such as reaching target groups through chatrooms, sending e-mails to pre-established lists of participants, or posting banners on popular websites [94,95]; however, we will not use these latter strategies in our study. According to Noseck *et al*. [95], even if posting advertising banners is a popular way of promoting a study, it remains a costly means of recruitment and ‘is not the most effective at netting traffic’ ([95], p. 167).

One of the risks that remain difficult to control or prevent in a virtual environment is having the same person participate more than once in a given study [93,95,96]. Although the incidence of this happening has been shown to be small, at 3%, [93,97], certain strategies can be used to detect or prevent it and reduce the risk of its occurrence, including warning participants to register only once, asking for an email address and a password at registration, and filtering data that seem to be identical[93,95,96].

The ethical aspects of online studies have been discussed by various authors [98-101]. The topic has received special attention because of the online research environment in itself, where there’s no direct interaction between researchers and participants [95,96]. Among other things, consent to participate can be presented in the form of a statement to be read and checked off before clicking on a button labeled ‘I accept’. A button labeled ‘withdraw’ or ‘quit the study’ [95] will also be accessible to allow participants the freedom to drop out of the study at any time. As proposed by Hewson [99] and Nosek *et al*. [95], a ‘debriefing page’ and contact information for a resource person in the event of questions or problems will also be provided. The information must be presented in such a way as to properly inform participants but without overwhelming them with data, which could cause difficulties and discourage subjects from participating.

The security and confidentiality of electronic data in online studies are serious concerns that necessitate the implementation of stringent measures. The data collected through the online questionnaires will be stored on a secure server located at the research center where the research work is carried out. Only system administrators will have access to the data on the server. To protect the identity of participants, only an email address and a pseudonym will be requested from participants, as this information is necessary to ensure follow-up and disseminate results, as pointed out by Michalak and Szabo [100]. Using a firewall, encrypting the data, protecting passwords, and separating the sociodemographic data from the experimental data (linking them through a code) reduces the risk of an unauthorized third party accessing confidential content [95,101]. A database has been planned to support the subsequent direct transfer of the data to analysis software (the SPSS package; SPSS Inc., Chicago, IL, USA) in order to facilitate data analysis.

As emphasized by Bull *et al*. [94], online longitudinal evaluations entail following up participants and completing various measures. According to Bull *et al.*[94] and Bennett and Glasgow [92], online studies have a lower retention rate than that of traditional studies, and attrition rates of 40% are not uncommon. However, Schubart *et al.*[102] and Bull *et al*. [103] highlighted a number of elements that foster a high retention rate in online studies, including the availability of a health professional to provide feedback, the dynamic qualities of the study website, and the inclusion of a clinician coach, such as a nurse, in the intervention. All of these will be considered in this study.

For the purpose of encouraging participants to continue with the study, reminder e-mails (maximum of three to four) will be sent out at 7-day intervals prior to measurement. Bull and colleagues [94] noted that e-mails alone were not sufficient to communicate with participants, and that a variety of communication modes should be used. They suggested that participants should be asked to provide other contact details such as home and mobile telephone numbers, and a home address. According to these authors, a balance must be struck between guaranteeing confidentiality and ensuring follow-up. Because the technology we plan to use is complex and can present many problems and bugs, we plan to assign a resource person (technical support) to help users in this regard. According to Paul and colleagues [101], this constitutes a key source of support if the research budget allows it.

A research project that unfolds entirely online necessitates that all parties share an understanding of the specific terminology used by the various experts involved and of the role played by the professionals in each of the project’s teams (computer programming, multimedia, clinical). It is necessary to ‘think virtual’, that is, to make sure that procedures applied in the real world are operational online. Transposing research procedures to an entirely virtual research intervention entails anticipating the entire sequence of participation and follow-up of the target persons. Making this shift is not easy. Indeed, the absence of a common language between research, clinical, and web media teams, as well as a mutual misunderstanding of the needs of each group (researchers versus tech support teams, for instance), calls for a great deal of clarification and numerous meetings to make the technical operations required by the project possible. This collaboration between researchers from clinical disciplines (nursing and medicine), experts in behavioral and educational sciences, and information technology and media experts is crucial to the development of innovative solutions to supplying and delivering services to those who need them.

However, without the contribution of community partners and other clinical collaborators, such a study could not be carried out easily. Their support and expertise are invaluable at all levels, particularly in planning and developing the different stages of the online study (for example, using testimonials was our partners’ idea). Our partners will also be involved in promoting the study, recruiting participants, and ultimately transferring and implementing the virtual intervention.

